### Assessment points

Online assessments for the core study period will occur at 0 (baseline), 3 (mid-intervention), 6 (post-intervention) and 10 weeks (follow-up) from randomisation. Waitlist control participants will receive access to the digital CBT app after the follow-up assessment point (after 10 weeks from randomisation). In order to understand if effects persist over time, participants randomised to the intervention arm will also be invited to complete an optional longer-term uncontrolled assessment online at 6 months from randomisation without compensation. Table 1 presents details of the self-reported measures administered at each assessment point. After randomisation, participants will have up to 2 weeks to complete each questionnaire assessment battery. The trial coordinator will make every reasonable effort to follow the participant for the entire study period (from consent to the final follow-up assessment) using both email and telephone calls. To promote outcome data completeness, where necessary participants will be reminded to complete assessments first by a daily email reminder for up to 3 days and then by telephone for each overdue assessment. Participants who do not complete a study assessment will not be withdrawn from the study and will continue to be asked to complete any subsequent assessments. All online surveys will be hosted and stored on Qualtrics. Potential errors with data entry will be minimised as data will be entered by participants online.

**Table 1 Tab1:** Administered self-report measures and timeline

Measure	Screen	Study period			
		Baseline (week 0) and randomisation	Mid-intervention (week 3)	Post-intervention (week 6)	Follow-up (week 10)^**a**^
Basic screening questions (age, pregnancy)	X				
Medical and psychiatric history questions	X				
Prescription medication use	X				
MINI for GAD	X				
GAD-7	X		X	X	X
Demographic questions		X			
Credibility/expectancy questionnaire		X			
PHQ-9		X	X	X	X
PSWQ		X	X	X	X
SCI-8		X	X	X	X
WEMWBS		X		X	X
Patient-Generated Index		X		X	X
Modified symptom checklist				X	
Treatment satisfaction questions^b^				X	
Concomitant treatment		X	X	X	X

*GAD* generalised anxiety disorder, *GAD-7* seven-item Generalised Anxiety Disorder questionnaire, *MINI* Mini-International Neuropsychiatric Interview, *PHQ-9* nine-item Patient Health Questionnaire, *PSWQ* Penn State Worry Questionnaire, *SCI-8* eight-item Sleep Condition Indicator, *WEMWBS* Warwick–Edinburgh Mental Wellbeing Scale

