### Procedure

The Consolidated Standards of Reporting Trials (CONSORT; [38]) diagram displaying participant flow through the trial is shown in Fig. 1. Participants who respond to advertisements will be directed to the online participant information sheet and asked to consent to and complete an online screening survey as a first step in assessing eligibility against inclusion and exclusion criteria. Screening questions will assess age, GAD symptom severity (GAD-7), GAD diagnosis (MINI for GAD), medical and psychiatric history, prescription medication use and pregnancy. Eligible participants who meet inclusion criteria assessed above by the online screening survey will then be contacted by a member of the research team to take part in a brief 10-min telephone call. During this call, study procedures will be explained, any questions about the study will be answered, and we will verify participant reports of GAD against criteria from the Structured Clinical Interview for DSM-5 [39], ensuring that the participant feels their GAD symptoms are their current primary area of concern. All potential participants were informed (through study advertising, the participant information sheet and during the telephone conversation) that they should aim to use the app daily throughout the study period. Eligible participants who are willing to participate are then emailed a link to the online consent form.

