**Fig. 1 Fig1:**
[figure not shown]
Summary of the trial design for the DigitaL Therapy for Anxiety (DeLTA) study. CBT cognitive behavioural therapy

Participants who consent will be allocated a unique identification code to use when completing all subsequent online surveys to ensure that identifiable information provided as part of consent is not directly linked to survey responses. This unique identification code will be used for data files to ensure confidentiality. Participants will receive an email asking them to complete an online baseline survey containing a battery of self-report measures (see Table 1). Upon completion of the baseline survey, participants will be automatically randomised to either the digital CBT or waitlist control condition and informed of their allocation by automated email. All participants allocated to digital CBT will receive immediate access to the intervention and access will not be withdrawn (i.e. participants are welcome to continue using the app after conclusion of their participation in the study). All waitlist control participants will be given access to digital CBT after the final controlled follow-up assessment point (after 10 weeks from randomisation).

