#### Assessment of safety

We will record the occurrence of any serious adverse events or adverse events reported to the trial coordinator at any point from study entry until the participant has left the study. A serious adverse event is defined as any untoward medical occurrence that is believed by the investigators to be causally related to digital CBT and results in any of the following: life-threatening condition (that is, immediate risk of death); or severe or permanent disability, prolonged hospitalisation, or a significant hazard as determined by the trial management committee. The study will monitor for potential adverse effects through frequent Anxiety and Depression symptom questionnaires (GAD-7 and PHQ-9). A modified symptom checklist [51] will also be used to document potential somatic and psychological side effects. The questionnaire is administered at post-intervention only and asks participants to indicate whether or not they experienced any of 14 pre-specified unwanted symptoms (e.g. low mood, feeling agitated) or other non-listed unwanted symptoms at any point during the treatment period. The original version of the symptom checklist asks participants to report on the development of any unwanted symptoms while taking part in a programme. In order to ensure that the questionnaire is also applicable to the waitlist condition (who will not have access to the programme until 10 weeks after randomisation), the questionnaire was modified after recruitment start to ask whether or not participants developed any unwanted symptoms more generally over the last 6 weeks. The questionnaire also asks to what extent any unwanted symptoms interfered with everyday functioning using a five-point Likert scale from 0 (“not at all”) to 4 (“very much”).

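### The once-only side-effect checklist looks back six weeks from the day it is completed, so late completers lose early app use, and no checklist covers the controlled weeks 6 to 10

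*Protocol article*

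**What the plan says.** All references are to the protocol article.

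- **Number of administrations.** Assessment of safety: "The questionnaire is administered at post-intervention only". Table 1 agrees, with a single mark for the "Modified symptom checklist" at week 6 and none at week 3 or week 10.
- **Period covered, as described.** The same section says participants indicate whether they had any of 14 listed symptoms or "other non-listed unwanted symptoms at any point during the treatment period".
- **Period covered, as asked.** To make the item usable in the waitlist arm, "the questionnaire was modified after recruitment start to ask whether or not participants developed any unwanted symptoms more generally over the last 6 weeks".
- **Timing of completion.** Assessment points: "After randomisation, participants will have up to 2 weeks to complete each questionnaire assessment battery".
- **App use.** Procedure says that all potential participants were told "that they should aim to use the app daily throughout the study period". It also says: "All participants allocated to digital CBT will receive immediate access to the intervention and access will not be withdrawn".
- **Length of the study period.** Assessment points takes it from consent to the last follow-up. Table 1 runs its study-period columns from week 0 to week 10, and Participants ends the core period after 10 weeks. Waitlist participants get the app only after that.
- **Other safety capture.** Adverse events reported to the trial coordinator are recorded until the participant leaves the study. GAD-7 and PHQ-9 are named as monitoring for adverse effects and are scheduled at weeks 3, 6 and 10.

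**The concern.** The checklist is described by one period and asked by another. The description refers to the treatment period, which begins when app access begins, at randomisation. The question refers to a fixed six weeks ending on the day of completion. The two coincide only if the form is completed exactly at week 6. With a two-week window, and with email and telephone reminders planned for overdue assessments, some late completion is to be expected. The time then lost is the start of app use, when a participant first meets the techniques.

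There is also a question of reach. The last paragraphs of Background justify the waitlist comparator as a test of safety as well as efficacy. Weeks 6 to 10 are still a randomised comparison: one arm has the app and is asked to use it daily, and the other has no access. The checklist is the scheduled instrument meant to document somatic and psychological side effects, and it is not given in that interval.

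At stake is the completeness of the between-arm description of unwanted symptoms. If app-related symptoms tend to occur early, late completion would remove them mainly from the intervention arm and make the arms look more alike. The primary and secondary efficacy outcomes are not affected.

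**Working it through.** The article states no figure for coverage, so there is none to reproduce. The check compares the interval that the question covers with the intervals of interest.

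**Inputs**
- Look-back: 6 weeks, ending at completion (Assessment of safety).
- Nominal assessment: week 6 from randomisation (Assessment points).
- Completion window: 2 weeks (Assessment points). Assumption: it opens at week 6, so completion falls at week t with 6 ≤ t ≤ 8. The article does not say when it opens.
- App access in the intervention arm: from week 0, not withdrawn (Procedure).
- Controlled period: weeks 0 to 10 (Participants, Assessment points).

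**Step 1: coverage of weeks 0 to 6.** The question covers weeks t − 6 to t. Its overlap with weeks 0 to 6 is 6 − (t − 6) = 12 − t weeks, so the share missed is (t − 6)/6.

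| Completed at week | Look-back covers weeks | Covered of weeks 0–6 | Missed |
|---|---|---|---|
| 6 | 0–6 | 6/6 = 100% | 0% |
| 6.5 | 0.5–6.5 | 5.5/6 = 92% | 8% |
| 7 | 1–7 | 5/6 = 83% | 17% |
| 7.5 | 1.5–7.5 | 4.5/6 = 75% | 25% |
| 8 | 2–8 | 4/6 = 67% | 33% |

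The average loss over participants is (mean delay in weeks)/6. The article gives neither the share of late completers nor their delay, so only the range of 0% to 33% per participant can be stated.

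**Step 2: coverage of the 10-week controlled period.** For any t from 6 to 8 the six-week look-back lies wholly within weeks 0 to 10, so it covers 6/10 = 60% and leaves 40%. For an on-time completer the uncovered time is weeks 6 to 10. For a week-8 completer it is weeks 0 to 2 and weeks 8 to 10.

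Steps 1 and 2 use different reference periods and must not be added. If time after week 6 counts as exposure, a week-8 completer still reports on six exposed weeks, only shifted later. If it does not count, Step 2 falls away.

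**Step 3: is week 6 to 10 exposed time?** Daily use is advised for the study period; that period runs to the final follow-up; access is not withdrawn; the waitlist arm has no access until after week 10. Taken together, these make weeks 6 to 10 exposed in one arm and unexposed in the other. The labels post-intervention (week 6) and follow-up (week 10) point to a treatment period of weeks 0 to 6. The article does not define the treatment period against continuing use.

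**Step 4: what else covers the gaps?** GAD-7 and PHQ-9 each ask about the preceding 2 weeks, so week 3 samples weeks 1 to 3 and week 10 samples weeks 8 to 10. They measure anxiety and depressive symptoms. Adverse events are recorded throughout but depend on someone reporting them. Neither asks systematically about the checklist's 14 symptoms.

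**The case against.** The strongest reply is that the checklist does what it is said to do. Week 6 is called post-intervention throughout, so the treatment period is naturally weeks 0 to 6, and a participant who answers on time covers all of it. Nothing in the article promises checklist data for weeks 6 to 10. The 33% is a ceiling that applies only to the latest completers and depends on when the window opens; reminders exist to keep lateness down. The same look-back and window apply in both arms, so no difference between arms is built in.

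Most of this stands. A reader might infer that the checklist misses much of the exposure it claims to cover. The article does not support that: the loss is zero for on-time completers, and weeks 6 to 10 are outside the stated scope. A reader might also infer that the checklist is the only systematic measure of unwanted effects. That is also unsupported, because GAD-7 and PHQ-9 are named as safety monitoring and run to week 10 in both arms.

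A third tempting inference is that waitlist answers given before the trial modified its checklist will contaminate the comparison. The first week-6 batteries could not fall due before 13 September 2019 (2 August 2019 plus 42 days). The date of the change is not given, so the number affected may be zero, and the handling of any such answers belongs to the analysis plan, which is not at hand.

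The reply leaves two things unanswered. A look-back counted from completion still does not match "at any point during the treatment period" for anyone who answers late. And advised daily use in a controlled interval goes without the checklist when a battery is already being sent.

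**Conclusion.** The point holds as a modest weakness in safety measurement. The fixed look-back costs a participant between 0% and 33% of the week 0 to 6 period, depending on the completion date and assuming that the two-week window opens at week 6. The average cannot be calculated from the article.

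Separately, weeks 6 to 10 are controlled and exposed time in which somatic and other side effects are not asked about systematically. That is 4 of the 10 controlled weeks (40%). It is a limit of scope: the article does not contradict itself by leaving those weeks out, though it would be clearer if the treatment period were defined against continuing app use. Both parts are worth correcting because the correction is cheap.

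**What to change.** 1. Anchor the week-6 checklist to randomisation, for example 'since you were randomised'. If the wording should not change again in mid-trial, keep it and use the recorded completion dates to report the period that each answer actually covers.
2. Add the same checklist to the existing week-10 online battery in both arms, worded 'since your last questionnaire'.
3. State what the treatment period means given that app use continues after week 6.

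The cost is small: one short checklist (14 symptoms, any others, and the interference rating) in a battery that both arms already receive, and a minor amendment. The main drawback is that rewording the week-6 item while the trial is open creates a further version, so the version each participant received must be recorded and results reported by version. Reporting coverage from completion dates avoids that drawback but does not recover the early weeks that late completers were not asked about.

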#### Concomitant treatment

The administration of other interventions and medications to address GAD is not prohibited after randomisation. Concomitant treatment will be assessed using the following questions administered at all time points from baseline onwards. First, “How many days over the last 3 weeks did you see a treatment provider about your anxiety” and, if yes, “what type of treatment did you pursue?”; this is captured from predefined responses (e.g. “general advice from my family physician or general practitioner or cognitive behavioural therapy, etc.”). If participants select CBT, they will then be asked to select which techniques they have used from a further predefined list. This question was included after a modification was made by the ethical review committee after recruitment start. Second, participants will also be asked “How many days in the last 3 weeks have you taken medications for anxiety that were prescribed by your doctor or not prescribed by your doctor?” (with the follow-up question “Please list these medications and the dosage”).

### Data management

The trial investigators and the trial statistician will have access to the final cleaned dataset. The project dataset will be collected and stored online in the study web portal created for the study by Qualtrics Survey Software (Qualtrics, Provo, UT, USA), and all data will be password protected. Data integrity will be enforced through a variety of mechanisms including data rules, range checks and consistency checks against data already stored in the database. All data will be treated as confidential. To ensure confidentiality, data dispersed to project team members will be blinded of any identifying participant information. Questionnaire data will be de-identified by a unique coded participant identification number only (assigned at consent into the study) to maintain confidentiality. Participant data linkage information will be stored in a single digital file separate from questionnaire research data. This file will be encrypted and stored on a secure server with limited user access and password protection for members of the study team only. Minimal personal identifiable information (e.g. name, email) will be captured and will only be made accessible (password protected) to the research study team. These data will be deleted at the completion of the study on publication or public release of the results. We will only hold contact information of participants who give optional consent to being contacted again in the future and will retain these records for 7 years after the release of this work. The final anonymised research data will be archived with the Oxford Research Archive (ORA-Data) at the University of Oxford for longer term storage (at least 7 years) after publication or public release of the results.

### Statistical analysis

Analyses will be carried out using Stata [52]. In accordance with the CONSORT statement [38], we will report all participant flow in each arm (see Fig. 1). Descriptive statistics of participant recruitment, study dropout and intervention engagement will be reported. Baseline characteristics will be presented by randomised group and summarised by means and standard deviations for continuous measures, or number and percentage for categorical measures.

To test the primary hypothesis, treatment effects on GAD symptom severity (GAD-7) will be estimated using linear mixed models fitted to data at all core time points (baseline, 3 weeks mid-intervention, 6 weeks post-intervention, 10 weeks follow-up). Fixed effects will be baseline assessment for GAD-7, randomised group, time (categorical), and time by group interactions. Participant ID will be included as random intercepts to allow for repeated measures. Marginal treatment effects will be estimated for GAD-7 at each time point and reported separately as mean-adjusted differences in scores between the randomised treatment groups with 95% confidence intervals and two-sided *P* values. The analysis will use statistical techniques for handling missing data under a missing-at-random assumption. Secondary hypotheses will be tested using analogous analyses. For the binary secondary outcome (whether participants achieved remission and reliable remission on GAD-7, PHQ-9 and SCI-8 outcomes), the same approach will be followed using logistic mixed models. All primary and secondary analyses will be conducted on an intention-to-treat basis, including all participants who were randomised, with no planned interim analysis.

Additional sensitivity analyses will be conducted to test primary and secondary hypotheses using data from participants who receive and engage with the intervention, defined as those who: 1) download the app; 2) complete at least two modules of digital CBT; and 3) complete all modules. Separate sets of analyses will be conducted for each of these three categories of intervention completion.

Exploratory analyses will examine mechanisms underlying the effect of digital CBT compared to waitlist control on GAD symptom severity using causal mediation methods based on parametric regression models. This will examine whether changes in worry (PSWQ), depressive symptoms (PHQ-9) and sleep difficulty (SCI-8) during the intervention period (from baseline to 3 weeks mid-intervention) significantly mediate the effect of digital CBT compared to waitlist on changes in GAD symptom severity (GAD-7) from baseline to 6 weeks post-intervention. Exploratory moderation analyses will also be conducted to examine whether the between-group effect on GAD symptom severity is moderated by baseline variables (e.g. demographic variables, baseline levels of anxiety).

All analyses will be pre-specified in a detailed statistical analysis plan.

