### Sample size

The sample size calculation was conducted using G*Power 3 [31]. The study aims to recruit 242 participants with GAD, with 121 participants randomised to each arm. This recruitment target accounts for approximately 30% attrition, based on the range of dropout rates from previous RCTs comparing smartphone-based digital interventions for anxiety to waitlist (19% to 45%; [32–34]). The sample size was determined based on an estimated medium effect on post-intervention scores on the seven-item Generalised Anxiety Disorder questionnaire (GAD-7) (Cohen’s *d* = 0.50) between the digital CBT and waitlist arms, with 90% power, a 1:1 allocation ratio, and with *α* set at 0.05. The effect size is based on a recent meta-analysis of RCTs of smartphone-delivered psychological treatment for anxiety versus waitlist which demonstrated a small-to-moderate (Hedges’ *g* = 0.33) between-group post-intervention effect on anxiety symptoms when compared to any active or waitlist/inactive control condition [28]. When comparing smartphone interventions with only waitlist/inactive control conditions, Hedges’ *g* increased to 0.45. The effect size of 0.50 corresponds to a minimally clinically significant 2-point change on the GAD-7 and a standard deviation of 4 in this population [35].

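### The primary mixed model uses baseline GAD-7 as both an outcome row and a covariate, so the week-6 standard error is too small and the nominal 5% test runs at about 8–10%

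*Protocol article*

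**What the plan says.** In the Statistical analysis section of the protocol article, the primary analysis is fixed by three statements:

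- Outcome data: "linear mixed models fitted to data at all core time points (baseline, 3 weeks mid-intervention, 6 weeks post-intervention, 10 weeks follow-up"). Baseline is named in the list of fitted visits.
- Mean model: "Fixed effects will be baseline assessment for GAD-7, randomised group, time (categorical), and time by group interactions".
- Covariance: "Participant ID will be included as random intercepts to allow for repeated measures". No visit-specific variance, unstructured covariance or robust standard error is mentioned.

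Group differences are then to be reported at each time point with "95% confidence intervals and two-sided" P values. The continuous secondary outcomes follow the same route: "Secondary hypotheses will be tested using analogous analyses". The logistic mixed models for remission are also to follow this approach.

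Table 1 shows only one GAD-7 before randomisation (at screening), so the week-0 outcome row and the baseline covariate can only be the same measurement.

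**The concern.** A baseline score can be modelled as an outcome or conditioned on as a covariate. Doing both in one random-intercept model has three consequences.

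1. In the week-0 row the covariate reproduces the outcome, so its residual is only (1 − slope) × baseline, far smaller than any follow-up residual.
2. The model assumes one marginal variance for all visits, so the small week-0 residual is pooled with the week 3, 6 and 10 residuals and pulls the estimate down. The week-6 standard error is built from that average.
3. The single baseline slope becomes a mixture of 1 (the week-0 row) and the true follow-up slopes.

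This is the one confirmatory test, designed at alpha 0.05. An understated standard error means a superiority claim could be made on evidence that does not meet the stated level. The model would also report a treatment effect on baseline GAD-7 adjusted for baseline GAD-7, which has no meaning.

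**Working it through.** **Inputs from the article (Sample size).** Two-sided alpha 0.05; "with 90% power, a 1:1 allocation ratio"; effect "2-point change on the GAD-7 and a standard deviation of 4" (d = 0.50); "This recruitment target accounts for approximately 30% attrition"; 242 participants, 121 per arm.

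**Assumed, because the article does not give them.** Correlations between visits (0.3–0.7) and visit-specific SDs (4 throughout, or 3 at baseline and 4–5 later).

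**Step 1: reproduce the stated sample size.** n per arm = 2(1.960 + 1.282)² / 0.50² = 84.1, so 85 per arm and 170 in total; 170 / 0.7 = 242.9. The stated 242 is reproduced to rounding. Power with 242 × 0.7 = 169.4 completers is 90.2%. Thirty per cent missing at week 6 is therefore the case the trial itself plans for.

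**Step 2: closed form, complete data.** Take SD 4 and a common correlation ρ, with four rows per participant.

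- Pooled baseline slope: β = (1 + 3ρ)/4
- Residual variance, week 0: V₀ = 16(1 − β)²
- Residual variance, each later visit: V₁ = 16(1 − 2βρ + β²)
- Variance the model uses: (V₀ + 3V₁)/4; variance that applies at week 6: V₁
- Actual alpha = 2[1 − Φ(1.96 √ratio)], where ratio = model variance / V₁

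At ρ = 0.5: β = 0.625, V₀ = 2.25, V₁ = 12.25. Model variance = (2.25 + 36.75)/4 = 9.75. Ratio = 9.75/12.25 = 0.796. With 121 per arm the model SE is √(2 × 9.75/121) = 0.401, against a true √(2 × 12.25/121) = 0.450. Alpha = 2[1 − Φ(1.96 × 0.892)] = 8.0%.

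ρ = 0.3 gives 7.5% and ρ = 0.7 gives 8.5%. Baseline SD 3, later SD 4.5 and ρ = 0.4 give 8.7%. If the week-0 residual were exactly zero, the SE ratio would be √(3/4) = 0.87 and alpha 9.0%; that is the limit for equal variances at the later visits.

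**Step 3: secondary outcomes with baseline plus two visits (WEMWBS, Patient-Generated Index).** The same algebra with three rows gives 9.1%, 9.8% and 10.3% at ρ = 0.3, 0.5 and 0.7. The limit is √(2/3) = 0.82, or 11.0%.

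**Step 4: simulation under no effect.** 242 randomised, random-intercept fit, week-6 contrast rejected at |z| > 1.96, 8,000 trials per scenario (Monte Carlo error about 0.3 points). Missingness is completely at random: 15% at week 3 and 30% at weeks 6 and 10.

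| Scenario | Data | Model SE / true SE | Alpha as written | Alpha, weeks 3, 6, 10 only |
|---|---|---|---|---|
| SD 4, ρ 0.5 | complete | 0.399/0.452 = 0.88 | 8.5% | 5.1% |
| SD 4, ρ 0.7 | complete | 0.323/0.369 = 0.88 | 8.9% | 5.3% |
| SD 3 then 4.5, ρ 0.4 | complete | 0.462/0.534 = 0.87 | 9.0% | 5.0% |
| Baseline truncated at 10 | complete | 0.440/0.506 = 0.87 | 9.1% | 5.2% |
| SD 4, ρ 0.3 | 30% missing | 0.523/0.609 = 0.86 | 9.5% | 5.4% |
| SD 4, ρ 0.5 | 30% missing | 0.459/0.548 = 0.84 | 10.3% | 5.7% |
| SD 4, ρ 0.7 | 30% missing | 0.368/0.443 = 0.83 | 10.5% | 5.1% |
| SD 3 then 4.5, ρ 0.4 | 30% missing | 0.527/0.631 = 0.84 | 10.5% | 5.1% |
| Baseline truncated at 10 | 30% missing | 0.500/0.612 = 0.82 | 10.7% | 5.3% |
| SD 4, decaying ρ | 30% missing | 0.451/0.551 = 0.82 | 10.8% | 5.8% |
| SD 3, 4, 5, 5, decaying ρ | complete | 0.457/0.561 = 0.81 | 10.9% | 6.6% |
| SD 3, 4, 5, 5, decaying ρ | 30% missing | 0.505/0.658 = 0.77 | 13.3% | 7.1% |

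Attrition makes it worse because everyone has a baseline row: its share of all rows rises from 1/4 = 25% to 1/(1 + 0.85 + 0.70 + 0.70) = 31%.

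Smaller REML runs (2,000 trials each, Monte Carlo error 0.5–0.7 points) gave as little as 6.2% with complete data and 8.5–10.5% with 30% missing. A 40,000-trial REML run at SD 4 and ρ = 0.5, complete data, gave 7.9%, in line with the closed form.

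**The case against.** **The sentence may only be misworded.** Baseline data also enter a model when they enter only as a covariate, and two features favour that reading. A baseline-adjusted effect on baseline is meaningless. And since entry requires GAD-7 of 10 or more while remission is a score below 10, a baseline row in the GAD-7 remission model would contain no remitters. On that reading the test is close to 5%. This is a fair point about intent, but the text lists baseline explicitly among the fitted visits, so the published specification is the faulty model and needs correcting on either reading.

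**The SAP may deal with it.** The article promises a detailed SAP, and unstructured covariance or robust standard errors there would remove most of the problem. That is possible, but the article states a definite model with a random intercept only. The point concerns what is stated, not what is left out.

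**The size rests on assumptions.** This stands. Visit correlations and visit-specific SDs are not given, the limiting values (9% and 11%) are not reached exactly, and about 10% is reached mainly with attrition. The direction did not change in any scenario.

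**Unstructured covariance is a separate matter.** This also largely stands. Dropping the baseline row is the essential repair. The covariance change deals with the smaller excess (5.8–7.1%) that remains only if correlation decays or variance rises over time.

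**Conclusion.** The concern holds. As written, the primary model understates the week-6 standard error by about 12–13% with complete data and 14–18% with the planned 30% attrition in most scenarios (up to 23% in the most extreme). The nominal 5% test then runs at about 7.5–9% and 9.5–11% respectively, so about 8–10% is a fair summary, with 13% in the most extreme case and about 6% in the most favourable small run. A nominal 95% interval covers about 90–92%.

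These figures assume correlations of 0.3–0.7, SD 3–5 depending on visit, and data missing completely at random. The treatment estimate is unbiased under no effect; the fault lies in the standard error, interval and P value. Because it affects the only confirmatory test and carries over to every continuous secondary outcome, it must be corrected before analysis.

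**What to change.** State one role for baseline, in both the protocol and the SAP.

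- **Preferred:** fit the model to weeks 3, 6 and 10 only, with fixed effects for baseline score, baseline-by-time, group, categorical time and group-by-time. Replace the random intercept by an unstructured residual covariance, estimated by REML (Stata: `mixed` with `residuals(unstructured, t(week))` and no random intercept).
- **Alternative:** keep baseline in the outcome vector, remove it as a covariate, constrain the arms to a common baseline mean and use an unstructured covariance.

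Report treatment effects at weeks 3, 6 and 10 only. Apply the same rule to all continuous secondary outcomes (weeks 6 and 10 for WEMWBS and the Patient-Generated Index), and leave baseline rows out of the remission models. If the random intercept is kept, removing the baseline row is the minimum change.

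The cost is two sentences and one line of code, with no new data. Confidence intervals become about 10–20% wider (for example 0.443/0.399 = 1.11 with complete data and 0.626/0.527 = 1.19 with 30% missing), which is their correct width.
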